### Oversight and monitoring {5d, 21a, 22, 23 and 25}

A Trial Management Group comprising of all protocol contributors will meet at least quarterly during the recruitment phase with a view to reviewing targets and progress made. Additional meetings will be arranged as and when required. The group will also discuss interpretation of the findings and dissemination plans for the trial. There will be no data monitoring committee (DMC) due to the low-risk nature of the intervention.

All adverse events arising in either group will be documented and reported. This includes but is not limited to events that require further medical attention or hospitalisation. Adverse events will be recorded in an adverse events or serious adverse events log in the investigator site file and reported to the sponsor. Adverse events will be explored and categorised as related or unrelated to the trial intervention.

Protocol amendments will be submitted to the sponsor for approval prior to submission to the NHS REC. For any amendments, the CI, in agreement with the sponsor, will use the ‘Amendment Tool’ Excel template to categorise the amendment as A, B, or C and describe both the amendment and the rationale. Following completion of the declaration, this will then be submitted online alongside supporting documentation via the IRAS portal for consideration.

After the amendment has been submitted online, it will be shared with relevant personnel at the participating organisation. The email, with the completed and locked Amendment Tool and any amended documents attached, will be forwarded to the University Hospitals of Leicester NHS Trust R&D Office and local research team. Amendments will not be implemented until the approval for the amendment has been issued. Amendment history will be kept within the site file to aid identification of the most recent protocol version. Participants will be re-consented if significant changes are made to the study protocol.

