### Face-to-face rehabilitation (intervention) {11a and 11c}

Individuals will complete an individualised symptom-titrated programme of exercise, education, and self-management for 6 weeks. The programme will comprise two supervised sessions per week delivered by healthcare professionals.

Six weeks have been purposefully selected as the intervention period to align with current clinical provision in Leicester. Aligning the intervention period with that used clinically will consolidate clinical expertise and support implementation.

The rehabilitation programme will consist of aerobic exercise (i.e. treadmill/ground walking at 80% of the incremental shuttle walk test (ISWT) speed where tolerated and lower-limb cycling on a static bike) and resistance exercise training (upper and lower limb strength exercises). The exercise intensity and duration will be tailored to the individual’s current abilities, assessed in their first visit.

In addition to the supervised sessions, patients will be asked to perform home-based exercise sessions which align with the supervised sessions to include the following: daily walking, three aerobic exercise sessions, and one resistance exercise session each week. Participants will be asked to record their progress in a self-reported diary, which will be used in conjunction with self-reported symptoms at the face-to-face sessions for the delivering clinicians to monitor symptoms and guide exercise modifications and progression.

Each rehabilitation session will include an educational discussion (approx. 30–60 min) delivered by a member of the multidisciplinary team. These discussions will be facilitated by information sheets saved from the Your COVID Recovery (YCR) website repository. Topics covered will include the following: getting moving again, managing activities of daily living, breathlessness, fatigue management, and recognising symptoms of worsening in response to exercise, fear and anxiety, mood and coping, memory and concentration, cough, eating well, sleep hygiene, goal setting, headaches, managing symptom exacerbation and fluctuations, and returning to work. At the end of each session, there will be an opportunity for discussion and question and answer.

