Signs of post-exertional malaise and post-exertional symptom exacerbation will be monitored using the DePaul Symptom Questionnaire–Short Form (DSQ-SF) [25], modified Borg breathless scale [26], and Borg rate of perceived exertion (RPE) [27], and results were discussed by the healthcare professional with the participant at the start of each session. Adjustments to the exercise programme, or onward referral, will be made as necessary, and patients may be removed from the study if adverse events occur.

Clinical staff responsible for delivering the intervention have become experts in this now well-established intervention. Training will be provided to any new staff, and a competency scheme is in place to ensure there is standardisation of care.

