### Usual care (control) {6b}

Participants in the control arm will receive usual care for 6 weeks. Routine clinical care will continue, such as medical follow-up, mental health service provision, and other specialist services.

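### Raw adverse-event counts are open to detection bias: symptom worsening is reviewed at up to 12 rehabilitation sessions, with no interim trial contact described for controls

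*Protocol article*

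**What the plan says.** **Both arms.** Oversight and monitoring states: "All adverse events arising in either group will be documented and reported". It adds that this is not limited to events needing medical attention or hospital admission. Events go into a log, are reported to the sponsor and are classed as related or unrelated to the intervention. The article gives no method of eliciting them, no recall period and no contact schedule.

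**Rehabilitation arm.** The intervention section states: "The programme will comprise two supervised sessions per week delivered by healthcare professionals". The programme lasts 6 weeks. Post-exertional malaise and symptom exacerbation are monitored with the DSQ-SF, the modified Borg breathlessness scale and the Borg exertion scale, and "results were discussed by the healthcare professional with the participant at the start of each session". In addition, "Participants will be asked to record their progress in a self-reported diary", which is read alongside self-reported symptoms at the sessions. The education topics include recognising worsening after exercise.

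**Control arm.** Usual care (control) states: "Participants in the control arm will receive usual care for 6 weeks". Routine care continues, including medical follow-up.

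**Common assessments.** Table 2 marks the DSQ-SF and the other symptom and quality-of-life scales at enrolment and at 6–8 weeks. It has no adverse-event row, and it marks no DSQ-SF in the intervention column.

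**The concern.** The promise covers events of any severity in both arms, but the opportunities to find the milder ones differ sharply. A symptom flare in a rehabilitation participant can come up at the next session, within days. The same flare in a control has no described route into the trial log until follow-up, unless the participant volunteers it or it reaches a clinic that passes it on.

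Controls can be expected to have flares: the Background calls Long Covid symptoms often unpredictable. The Discussion notes that patients who feel dismissed may not present to healthcare, so routine care may not pick these flares up.

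This matters because the section on discontinuing or modifying interventions gives particular attention to post-exertional worsening, and the trial has neither formal stopping rules nor a data monitoring committee. The adverse-event log is thus a main safety output. If the two columns of a harms table come from different intensities of questioning, an excess under rehabilitation can be read as harm when it is only closer observation. Equally, a real excess can be dismissed as closer observation.

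**Working it through.** The plan gives no figure to reproduce here. The check compares contact schedules and then works out what unequal detection does to a count.

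**Step 1: contacts at which worsening could be found**

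| | Rehabilitation | Control |
|---|---|---|
| Common trial assessments (Table 2) | 2 | 2 |
| Interim trial symptom reviews described | 2 per week × 6 weeks = up to 12 | 0 |
| Diary read with symptoms at sessions | yes | not described |
| Routine clinical care | yes | yes |

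**Step 2: effect on a raw count.** Let *n* be the number per arm, *p* the true event risk (the same in both arms), and *d*R and *d*C the shares of events detected in rehabilitation and control.

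- Recorded events: *n·p·d*R and *n·p·d*C.
- Apparent risk ratio with no true difference: *d*R / *d*C.

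The recruitment target of 56 with 1:1 allocation gives *n* = 28. The document gives no *p* and no detection rates, so the values below are assumptions for illustration. With *p* = 20%, true events are 28 × 0.20 = 5.6 per arm.

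| *d*R | *d*C | Recorded events | Apparent risk ratio |
|---|---|---|---|
| 100% | 100% | 5.6 v 5.6 | 1.00 |
| 100% | 75% | 5.6 v 4.2 | 1.33 |
| 90% | 60% | 5.0 v 3.4 | 1.50 |
| 100% | 50% | 5.6 v 2.8 | 2.00 |
| 90% | 40% | 5.0 v 2.2 | 2.25 |
| 100% | 25% | 5.6 v 1.4 | 4.00 |

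The ratio does not depend on *p*. It only restates the chosen detection rates, and the range includes no bias at all.

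**Step 3: would asking both arms at follow-up suffice?** Suppose the follow-up question captures a share *f* in both arms, and the sessions capture a further share *s* of what it misses. Rehabilitation detection is then *f* + (1 − *f*)*s*, and the apparent ratio is 1 + *s*(1 − *f*)/*f*. This exceeds 1 unless *s* = 0 or *f* = 1. For example, *f* = 0.60 and *s* = 0.75 give 0.60 + 0.40 × 0.75 = 0.90, and 0.90/0.60 = 1.50. A common question therefore equalises the comparison only if session-only events are kept out of it.

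**Step 4: what the symmetric scales can show.** A two-sample *t*-test at two-sided 5% has 80% power for a standardised difference of about 0.76 with 28 per arm, and about 0.84 with 23 per arm. The common DSQ-SF comparison is thus available, but sensitive only to a large mean worsening.

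**Step 5: DSQ-SF in two places.** The intervention section names the DSQ-SF as a monitoring tool whose results are "discussed by the healthcare professional with the participant at the start of each session". Read naturally, this means it is repeated during the programme. Table 2 marks it only before and after. The two need to agree.

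**The case against.** There is a fair case on the other side.

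- **No between-arm test of adverse events is planned.** Statistical analysis specifies none, and no objective is a comparative safety objective. This stands, so the point concerns how the reported counts will be read and not a faulty test. Counts reported for two arms will still be compared.
- **The article condenses a fuller protocol.** That document may set out how events are elicited, and the silence here is not itself an error. This also stands. But Step 3 shows that a common follow-up question would not make total counts comparable while session findings are added to one arm.
- **Session monitoring exists to adjust exercise or refer onward.** Nothing says that session scores are logged as events. True, but a promise to document all events makes it likely that worsening seen at a session will be. If staff instead treat flares as an expected part of titration, the over-count shrinks. Hence the direction is *most likely*, not certain.
- **Controls are not out of sight.** Routine follow-up continues, and Trial design and setting says medical support is available throughout. This stands in part: no schedule is given, nor a route from that care into the trial log.

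A reader might infer that the trial cannot show whether exercise worsens symptoms. The document does not support that. The DSQ-SF, C19-YRS, FACIT-Fatigue, MRC dyspnoea, PHQ-9, GAD-7 and EQ-5D-5L are taken in both arms at the same two times, and blinded staff conduct the post-intervention assessments. The limits are that participants are unblinded, the scales are self-reported and the secondary outcomes are not powered. In addition, participants suspended for post-exertional worsening could be lost from this comparison in one arm if their follow-up stops, which the article does not settle.

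**Conclusion.** The point holds as a cheap improvement. Ascertainment is unequal as described: up to 12 active symptom reviews in one arm, and no interim trial contact described in the other. Raw between-arm counts are therefore open to detection bias, most likely towards over-counting in the rehabilitation arm.

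The size is unknown. Ratios such as 1.5 or 2.25 follow only from assumed detection rates and should not be quoted as estimates. It would also go too far to say that the counts *are* biased by a known amount, or that controls have no contact with anyone: the document supports only that no interim *trial* contact is described.

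The conclusion rests on two assumptions: that at least some worsening found at sessions enters the adverse-event log, and that the full protocol does not already separate session-only events from events elicited in the same way in both arms. If it does, stating so in the report would suffice.

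**What to change.** 1. At the existing 6–8 week visit, give both arms the same short adverse-event and symptom-worsening form covering the whole period since baseline, and add it to Table 2. Make it self-completed, so that the blinded assessor does not hear about sessions.
2. Base any between-arm harms comparison on that form and on the enrolment and follow-up DSQ-SF.
3. Still log every event, but report those found only at rehabilitation sessions separately, as intervention-arm monitoring data.
4. Reconcile Table 2 with the intervention section on whether the DSQ-SF is repeated during the programme.

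**Cost.** One form at a visit already scheduled, one table row and a line in the safety reporting.

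**Downside.** Recall over 6–8 weeks is imperfect and may still differ between arms, because only the rehabilitation arm is described as keeping a diary, is taught to recognise worsening and discusses symptoms at sessions. The change reduces the asymmetry but does not remove it, and the report should say so.

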### Patient and public involvement and engagement (PPIE)

Patient and public involvement and engagement (PPIE) is recognised as an essential aspect of the research process. Patients have been involved from conception of trial design and will continue to be involved throughout the delivery phases and to optimise dissemination. This involvement has been shaped by the ‘UK Standards for Public Involvement’ [51]. The research team and PPIE group will continue to work together in a mutually respectful partnership, with contributions recognised and valued and suggestions incorporated. Participants receive high street gift vouchers to the value outlined in the NIHR public contributor payment policy [52], in recognition of their time, acknowledgement in resultant publications, and reimbursement of expenses for attending meetings face to face.

PPIE will continue throughout the recruitment and data collection period by means of a patient advisory group who will meet regularly and a representative who has volunteered to sit as a member of the Trial Management Group (author [name]). Advice will be sought on the content of the proposed topic guide, which will be utilised in both qualitative components with respect to accessibility of language, question relevance, and appropriateness.

During the results analysis and dissemination phases, the broader PPIE committee will be consulted and suggestions sought to translate the findings to ensure they are accessible and land appropriately with those who would benefit. This may include plain language communications to support groups and the wider patient community.

## Discussion

The purpose of this study is to determine whether face-to-face exercise-based rehabilitation (‘the intervention’) is effective and acceptable for Long Covid patients who have not been hospitalised, when compared to usual care alone. The mixed-methods research design comprises a randomised controlled trial (RCT) with an embedded qualitative evaluation with framed questions to investigate acceptability. Quantitative data alone would be insufficient to answer the research question; therefore, qualitative and quantitative approaches will be integrated to build a more comprehensive understanding.

There have been attempts to reduce the influence of bias; however, some processes are more difficult to mitigate. For example, it is not possible to mask trial participants or clinical delivery practitioners to treatment allocation, which may bias treatment effect estimates. With regard to selection bias and the recruitment strategy, it is imperative to recruit from the medically led Long Covid assessment service to ensure medical suitability and therefore safety. However, there is research to suggest people with Long Covid feel unsupported, disbelieved, and dismissed by healthcare professionals [53], which may influence who presents to healthcare and are therefore screened for inclusion in this study.

If meeting recruitment targets proves challenging, there are mitigations in place to approach previous patients who have expressed an interest in research and have consented to be contacted about future research opportunities. It is anticipated that rehabilitation drop-outs for the purposes of qualitative interviews will be more challenging to invite; however, there will be an effort made by the researchers to seek further engagement by means of a telephone call for those who consented to be contacted or via their assessing clinician when attending for medical follow-ups.

The substantive contributions of those listed as authors on this protocol meet the criteria outlined by the International Committee of Medical Journal Editors (ICMJE) [54] and will be recognised through the granting of authorship on the final trial report. Professional writers will not be employed to assist at any stage in the research process.

### Dissemination plans {31a, 31b and 31c}

Dissemination will include peer-reviewed publication, conference presentations, presentations to the clinical team, and engagement with the media. In addition, we will disseminate via patient and public involvement and engagement (PPIE) both during and at the end of the project. Author [name] will draw together an overview of the research process in its entirety and subsequent findings to present to examiners as her thesis. Research participants will receive a lay summary after the results have been published. Anonymised quantitative and qualitative datasets generated will be available upon request (after all publications are completed).

## Trial status

Trial recruitment started in November 2024, and its estimated recruitment will continue until December 2025. The current protocol is version 1.2 of 04-02-2025.
